## Abstract

High-intensity functional concurrent training (HIFCT) has emerged as a form of training characterized by constantly varied functional movements adapted to individual fitness levels. Previous studies have reported positive effects on muscular strength, cardiorespiratory fitness, body composition, and psychological well-being; however, evidence regarding HIFCT interventions in school-aged children remains limited. Therefore, the aim of the present study protocol is to evaluate the effects of an 8-week HIFCT programme on muscular strength, cardiorespiratory fitness, body composition, anxiety, stress, and self-esteem in children aged 10–12 years. Physical fitness, anthropometric variables, and psychological outcomes will be assessed before and after the intervention using validated field-based tests and questionnaires. This study may provide novel evidence regarding the feasibility, safety, and potential effects of HIFCT programmes in the school setting. The study protocol was registered at ClinicalTrials.gov (NCT07552844) and approved by the Córdoba Research Ethics Committee (IMIBIC, Córdoba, Spain; protocol code SICEIA-2025-000408).

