### 2.9. Outcomes

All outcome variables will be assessed at baseline (pre-test) and immediately after the 8-week intervention period (post-test). The study will evaluate physical fitness, body composition, and psychological outcomes in children aged 10–12 years using validated field-based tests and questionnaires (Figure S2). All baseline and post-intervention assessments will be completed during a single evaluation session lasting approximately 60–90 min. To minimize fatigue, physical fitness tests will be administered in a standardized order with adequate recovery periods between assessments according to established testing protocols. Participants will receive standardized instructions and verbal encouragement throughout the testing session. Familiarization trials will be provided when required by the testing protocol to ensure adequate understanding of the procedures and to promote valid test performance. Before the strength assessments, all participants will perform a standardized warm-up protocol consisting of: (i) a general warm-up including light running, skipping, heel-to-glute movements, arm circles, wrist and ankle rotations, lunges, and changes in direction; (ii) a specific warm-up for jump including controlled squats, low-intensity jumps, and lunges with trunk rotation; (iii) a specific warm-up for handgrip dynamometry involving squeezing a rubber ball and wrist flexion-extension exercises; and (iv) a specific warm-up for the medicine ball throw including shoulder rotations, light medicine ball throws, and core activation exercises.

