##### Body Weight, Height, and Body Mass Index (BMI)

Body weight and height will be assessed according to the ALPHA-Fitness battery procedures [43]. Body weight will be measured using an electronic scale (Tanita RD-545; Tanita Corporation, Tokyo, Japan), and height will be measured using a portable stadiometer (SECA 213; Seca GmbH & Co. KG, Hamburg, Germany). Body mass index (BMI) will subsequently be calculated as body weight in kilograms divided by height in meters squared (kg/m^2^).

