### 2.10. Sample Size and Power

Sample size estimation was performed using G*Power software version 3.1 [51] to ensure adequate statistical power to detect significant differences between the experimental and control groups in one of the primary outcomes of the study, maximal oxygen uptake (VO_2_max) estimated from the Course-Navette test. The calculation was based on two-tailed independent samples t-test using data reported by Alves et al. [52], who conducted a concurrent training intervention in children of similar age and intervention duration. In that study, the intervention group showed a mean increase of 1.7 mL·kg^−1^·min^−1^ in VO_2_max, whereas the control group showed a mean increase of 0.2 mL·kg^−1^·min^−1^. The pooled standard deviation of the change scores was calculated from the reported standard deviations of the intervention and control groups, 1.9 and 1.6, respectively, resulting in a pooled SD of approximately 1.76. Based on these values, the estimated standardized effect size was Cohen’s d = 0.86. Assuming an alpha level of 0.05, a statistical power of 0.80, and an allocation ratio of 1:1, the required sample size was estimated at 46 participants, with 23 participants per group. Considering a potential dropout rate of approximately 10–15%, the target recruitment will be increased to approximately 52–54 participants to maintain adequate statistical power throughout the study period.

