### 2.11. Statistical Analysis

Statistical analyses will be performed using IBM SPSS Statistics version 26.0 (IBM Corp., Armonk, NY, USA) or equivalent statistical software. Descriptive statistics will be calculated for all study variables and presented as mean ± standard deviation or median and interquartile range for continuous variables, and as frequencies and percentages for categorical variables. Data distribution will be checked using graphical methods and, when appropriate, the Shapiro–Wilk test. To account for the repeated-measures design, intervention effects will be analyzed using linear mixed-effects models. Separate models will be performed for each outcome, including group, time, and the group × time interaction as fixed effects, and participant ID as a random effect. Models will be adjusted for age, sex, and growth-related variables such as baseline height, body mass, and body mass index. Effect sizes will be calculated using partial eta squared (η^2^p) and interpreted as small (0.01), medium (0.06), or large (0.14) effects. In addition, Hedges’ g effect sizes will be calculated to estimate the magnitude of within-group changes and between-group differences in pre–post changes [53]. All effect-size estimates will be reported with 95% confidence intervals whenever appropriate.

Analyses will primarily follow the intention-to-treat principle. Linear mixed-effects models will be used because they allow the inclusion of all randomized participants with available observations and can accommodate incomplete outcome data under the missing-at-random assumption. Therefore, no imputation procedures are planned unless the amount or pattern of missing data suggests otherwise. A per-protocol analysis will also be conducted as a sensitivity analysis including participants who attend at least 80% of the intervention sessions.

Relevant changes in lifestyle-related factors during the intervention period, including the initiation of new structured physical activity outside the study, substantial changes in diet, sleep routines, or screen time, will be recorded when reported by families and considered when interpreting the results. Sensitivity analyses will be performed when appropriate and feasible.

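### Body mass, height and BMI are pre/post outcomes and also baseline covariates in their own models, so with the planned dropout their group × time standard errors come out too small

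*Protocol article*

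**What the plan says.** Section 2.9.2 (Secondary Outcomes) has an entry for body weight, height and BMI: "Body weight and height will be assessed according to the ALPHA-Fitness battery procedures". Section 2.9 has every outcome variable measured at pre-test and at post-test. The Abstract confirms this for anthropometry: "Physical fitness, anthropometric variables, and psychological outcomes will be assessed before and after the intervention using validated field-based tests and questionnaires".

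Section 2.11 then sets one model form for all of them: "Separate models will be performed for each outcome, including group, time, and the group × time interaction as fixed effects", with "participant ID as a random effect". Because time is a factor in the model, the pre-test value is a response row. The covariate rule that follows is "Models will be adjusted for age, sex, and growth-related variables such as baseline height, body mass, and body mass index", and it has no exception for models in which one of these variables is the response. The same section keeps every randomised child who has any observation, so a child without a post-test contributes the pre-test row alone. Section 2.10 plans for such children ("Considering a potential dropout rate of approximately 10–15"%) and raises recruitment from 46 to about 52–54.

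**The concern.** In the body mass model, the pre-test row of each child equals one of that child's covariates. The same is true of the height and BMI models. The covariate absorbs the pre-test rows, and nearly all the real variation is left in the post-test rows. A random-intercept model has a single residual variance and averages over the two kinds of row.

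With complete data the averaging does no harm. With dropout it does: each child without a post-test adds a residual near zero, which pulls the common variance down, and also adds to the count of rows behind the pre-test mean. The model then reports the precision it would have if every randomised child had supplied a change.

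Body composition is named in the aim and the hypothesis, and section 2.11 tests every outcome at p < 0.05. Intervals that are too narrow for BMI and body mass make a false finding on these outcomes more likely. The multiplicity caveat in section 2.11 does not cover this, because it concerns the number of tests and not the size of each one.

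**Working it through.** **Inputs from the protocol.** 46 completers needed, 52–54 recruited, 10–15% dropout, 1:1 allocation (2.10); two-sided 0.05; model and covariates as in 2.11.

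**The plan's own figures.** Pooled SD = √((1.9² + 1.6²)/2) = 1.756, and d = 1.5/1.756 = 0.854. A two-sample t-test then needs 23 per arm (power 0.809), so 46 in total, as stated. Losing 6 of 52 is 11.5%, and losing 8 of 54 is 14.8%. The sample size is sound and is not at issue.

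**Algebra.** Per arm, let n be randomised, m completers, and s² the variance of the post-test residual given baseline.

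- Pre-test rows: n residuals near 0. Post-test rows: m residuals with variance s².
- Common residual variance, with the random-intercept variance near zero: about m·s²/(n+m).
- Model variance of an arm's change: [m·s²/(n+m)] × (1/n + 1/m) = s²/n.
- True variance: s²/m.
- Model SE ÷ true SE = √(m/n). The unknown s cancels.

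Type I error is 2·(1 − Φ(1.96·√(m/n))):

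- 46 of 52: √(46/52) = 0.941, giving 6.5%.
- 46 of 54: √(46/54) = 0.923, giving 7.0%.
- Exactly 15% lost: √0.85 = 0.922, giving 7.1%.

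**Simulation 1** (27 per arm, no treatment effect, post-tests missing at random, REML, 4,000 runs per cell). Assumed, not in the documents: baseline BMI log-normal around 19 and BMI change SD 0.4 kg/m². Type I error, BMI / body mass:

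| Post-tests missing | Model as planned | Growth covariates removed, age and sex kept |
|---|---|---|
| 0 of 54 | 5.0% / 5.7% | 4.5% / 5.4% |
| 6 of 54 | 7.3% / 7.1% | 5.0% / 5.3% |
| 8 of 54 | 7.7% / 7.2% | 5.1% / 5.0% |

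The Monte Carlo standard error at 5% is √(0.05 × 0.95/4000) = 0.34 points, so the excess of about 2 points or more is not noise. Degrees of freedom based on completers lower the planned-model figures only to 6.9% / 6.7% (6 missing) and 7.3% / 6.9% (8 missing).

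**Simulation 2** (body mass only, 6,000 runs per cell, assumed pre–post correlation 0.95 / 0.98). The comparison model omits baseline body mass and BMI:

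| Completers of randomised | Planned: SE ÷ true SD | Planned: type I error | Comparison: type I error |
|---|---|---|---|
| 54 of 54 | 0.99 / 0.98 | 5.0% / 4.9% | 4.8% / 4.7% |
| 46 of 52 | 0.92 / 0.94 | 7.4% / 6.8% | 5.3% / 4.8% |
| 46 of 54 | 0.91 / 0.90 | 7.6% / 7.6% | 5.0% / 5.1% |

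Shorter runs at correlations 0.90 and 0.99 gave SE ratios of 0.93–0.94 and 0.89–0.91 at the two dropout levels. An unconstrained compound-symmetry covariance does not cure the problem (ratio 0.91–0.95). Modelling the post-test alone on its own baseline gives 4.8–5.2% with dropout.

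**Height.** A further simulation (54 randomised, assumed change SDs) included height, which behaved in the same way. Across outcomes the SE ratio was about 0.93 with 6 missing and 0.87–0.92 with 8 missing, with type I error of about 6–7% and 7–8.5%.

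**The case against.** The best defence is that the text is less fixed than it looks. The covariates are introduced as examples, the article condenses a fuller plan, and a sensible analyst would not enter a variable as a covariate in its own model. The secondary-outcomes heading is also loose: age, sex and session-level perceived exertion sit under it, so a listing there is weak evidence that height will have a treatment-effect model.

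This has some weight for height. It does not clear body mass or BMI. All three covariates are named, one model per outcome is stated, anthropometry is declared a pre/post measure, and no exception is written. An analysis plan could avoid the problem only by departing from the stated rule.

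The second line of defence is size. The excess is about two percentage points on two or three secondary outcomes, it needs dropout, and the estimate stays unbiased if dropout is completely at random. Body fat percentage, the other body-composition measure, is not among the covariates and is not touched. Take 17 tests, treated for illustration as independent: raising three from 5% to 7.5% moves the chance of at least one false positive from 1 − 0.95^17 = 58% to 1 − 0.95^14 × 0.925^3 = 61%. All of this stands. It limits the seriousness of the point but does not answer it.

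**Conclusion.** The concern holds. As written, section 2.11 puts the same measurement on both sides of the body mass, height and BMI models. At the planned dropout the group × time standard error is about 6–10% too small and the type I error is about 6.5–7.7%, with up to 8.5% in one simulation. A nominal 95% interval then covers about 92–93.5%.

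The size rests on dropout at random and on assumed pre–post correlations or change SDs. The direction does not depend on those spreads, because s cancels in the algebra and the SE ratio is similar for correlations from 0.90 to 0.99. With no dropout the problem effectively disappears.

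The point is of moderate weight. It should be corrected before analysis, but it does not touch the primary VO2max comparison or the sample size.

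**What to change.** Add one sentence to section 2.11: baseline height, body mass and BMI are not entered as covariates in models where one of them, or a quantity computed from them, is the response; those models are adjusted for age and sex only. The growth covariates stay for the fitness and psychological outcomes.

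Dropping only the outcome's own baseline is not a safe shortcut. Any two of the three variables determine the third, and entered together they come close to rebuilding it. Keeping baseline height in the body mass model, with body mass and BMI removed, is acceptable: this is the comparison model in the second simulation.

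The alternative is to model the post-test alone with its own baseline as covariate. It also restores the nominal error rate, but it leaves out children without a post-test, whom section 2.11 intends to keep. The age-and-sex mixed model fits the plan better for that reason.

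The cost is one sentence, with no new data, participants or procedures. The intervals for these outcomes become slightly wider, which is their correct width.

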## 3. Discussion

The present study protocol describes an 8-week HIFCT intervention designed to evaluate its effects on physical fitness, body composition, and psychological outcomes in school-aged children. Despite the growing scientific interest in HIFCT in pediatric populations, the available evidence remains limited and, in some cases, inconsistent [10,11,12]. Therefore, the present study seeks to contribute to the current literature by examining the feasibility, safety, and potential effects of a supervised and developmentally appropriate HIFCT programme in children aged 10–12 years.

Current evidence supports the role of regular physical activity in promoting physical and mental health during childhood and adolescence [2,5]. Previous studies have shown that structured exercise programmes can improve muscular strength, cardiorespiratory fitness, and body composition in youth populations [6]. In particular, resistance and concurrent training interventions have demonstrated positive effects on several components of physical fitness, although the magnitude of these adaptations appears to depend on factors such as training volume, intensity, participant characteristics, and programme design [9]. Within this context, HIFCT has emerged as a training modality that integrates functional multi-joint movements with strength- and cardiorespiratory-oriented stimuli within the same session [7,8].

Although several studies have reported favorable effects of HIFCT on physical performance and body composition [13], the available evidence remains heterogeneous. Differences in intervention duration, exercise intensity, participant characteristics, and methodological approaches make direct comparisons between studies difficult [10,11]. Furthermore, body composition outcomes during childhood may be influenced by factors beyond the intervention itself, including biological growth, dietary habits, sleep patterns, and habitual physical activity levels [5]. Consequently, additional well-designed studies are needed to better understand the potential effects of HIFCT in pediatric populations.

Another important aspect of the present protocol is the inclusion of psychological outcomes. Previous research suggests that physical activity may contribute to improvements in self-esteem and emotional well-being, as well as reductions in anxiety and stress symptoms among children and adolescents [15,16]. However, psychological responses to exercise are multifactorial and may depend on factors such as enjoyment, social support, perceived competence, motivational climate, and baseline psychological status [17]. Although some studies have reported positive psychological responses following HIFCT participation [19], findings remain inconclusive, highlighting the need for further investigation in this area.

The safety of HIFCT in children also warrants consideration. Current position statements indicate that resistance and functional training can be safely implemented in pediatric populations when programmes are appropriately supervised, individualized, and progressively prescribed [6,7]. Accordingly, the intervention proposed in the present study incorporates age-appropriate exercise selection, individualized adaptations, professional supervision, progressive overload, and systematic monitoring of adherence, exercise intensity, and adverse events throughout the intervention period.

One of the main strengths of this protocol is the comprehensive assessment of both physical and psychological outcomes within a single intervention. In addition, the programme has been specifically designed according to current recommendations for youth exercise training and includes detailed procedures regarding progression, monitoring, adherence, and participant safety. These characteristics may contribute to a better understanding of the feasibility and potential application of HIFCT in school-aged children.

Several limitations should also be acknowledged. First, the recruitment from a single educational center may limit the generalizability of the findings. Furthermore, the intervention will be conducted in a specialized HIFCT facility rather than within the school environment. Although this setting allows standardized implementation, professional supervision, and access to appropriate equipment, it may limit the ecological validity, scalability, and direct transferability of the findings to typical school-based physical activity programmes. Second, although the intervention duration was selected based on previous studies [15,16], it may be insufficient to detect stable adaptations in some body composition and psychological outcomes. Third, the use of a passive control group, while facilitating implementation under real-world school conditions, may limit the ability to distinguish the specific effects of the HIFCT intervention from the potential influence of increased supervision, social interaction, motivation, or participation in structured physical activity. Moreover, due to the nature of the intervention, participant and trainer blinding is not feasible, which may increase the risk of performance bias. In addition, although age- and growth-related variables will be considered in the analyses, the influence of normal growth and maturation during childhood cannot be completely excluded. Finally, the inclusion of multiple physical fitness, body composition, and psychological outcomes may increase the risk of type I error due to multiple statistical comparisons. Although this comprehensive assessment represents one of the strengths of the study, findings, particularly those related to secondary outcomes, will be interpreted with appropriate caution. Overall, the present study may provide valuable information regarding the feasibility, safety, and potential effects of HIFCT in school-aged children. The findings may contribute to the design of future randomized controlled trials and help inform evidence-based exercise recommendations for pediatric populations.

## 4. Conclusions

This study protocol describes an 8-week HIFCT intervention designed to evaluate its feasibility, safety, and potential effects on muscular strength, cardiorespiratory fitness, body composition, and psychological outcomes in school-aged children. Considering the increasing interest in HIFCT modalities in pediatric populations, this study may provide novel evidence regarding the implementation of developmentally appropriate HIFCT programme in children aged 10–12 years.

The integration of both physical and psychological outcomes represents one of the main strengths of the present protocol and may contribute to a broader understanding of the potential effects associated with HIFCT during childhood. Furthermore, the structured and supervised nature of the intervention may provide valuable information regarding the feasibility and safety of implementing age-appropriate HIFCT strategies in school and community settings.

The findings of this study may contribute to the growing evidence base on HIFCT in pediatric populations and help inform the design of future randomized controlled trials. Nevertheless, further large-scale and long-term studies will be required to confirm the findings and establish evidence-based recommendations regarding the use of HIFCT in children and adolescents.

## Figures and Tables

**Table 1 sports-14-00279-t001:** Structure and progression of the High-Intensity Functional Concurrent Training intervention during the 8-week study period.

Weeks	Section	General Description	Intensity
1–2	Warm-up	Dynamic stretching, skipping, coordination games	Moderate
1–2	Strength	Basic bodyweight movement patterns and introductory multi-joint exercises, with emphasis on technique instruction, movement control, and familiarisation with loaded exercise patterns when appropriate	Moderate
1–2	METCON	Short circuit-based or AMRAP tasks combining basic locomotor, coordination, jumping, and bodyweight conditioning activities	Moderate
3–4	Warm-up	Dynamic stretching, skipping, coordination games, and mobility drills.	Moderate
3–4	Strength	Introduction of light external loads and more complex multi-joint movement patterns with progressive technical instruction.	Moderate–vigorous
3–4	METCON	Progression to longer or denser conditioning circuits and AMRAP tasks with greater movement complexity and moderate use of jumping activities.	Moderate–vigorous
5–8	Warm-up	Dynamic stretching, skipping, coordination games, and mobility drills.	Moderate
5–8	Strength	Progressive external loading and greater movement complexity in multi-joint exercises.	Moderate–vigorous
5–8	METCON	Longer and more demanding AMRAPs or conditioning circuits, with greater jump complexity, exercise density, and overall conditioning demands when competency criteria are met.	Moderate–vigorous

Note: The intervention programme consisted of two weekly sessions specifically adapted to the age and physical capacities of the participants. Training load and exercise complexity progressively increased throughout the intervention period while maintaining participant safety and appropriate supervision. AMRAP = As Many Rounds As Possible; METCON = metabolic conditioning. All sessions were supervised by qualified professionals specialized in pediatric physical exercise and functional training.

**Table 2 sports-14-00279-t002:** High-Intensity Functional Concurrent Training intervention programme.

Session	Strength Component (Volume)	METCON Component	Intensity	Recovery
S1	Air squat (2 × 10). Focus on squat mechanics, trunk control, and movement familiarisation.	3 rounds: 10 squats, 10 lateral jumps, 20 m bear crawl	Moderate	1 min between rounds
S2	Incline or knee push-ups (2 × (8–10)). Progress range of motion as appropriate.	AMRAP 6 min: 5 push-ups, 10 lateral jumps, 5 spider walks	Moderate	Continuous
S3	Deadlift pattern with wooden bar/light training bar (2 × (8–10)). Focus on hip-hinge mechanics, trunk control, and movement coordination.	3 rounds: 10 deadlift-pattern reps, 20 jumps, 20 m run.	Moderate	30 s between rounds
S4	Elastic-band row or medicine ball row/pull variation ((2–3) × 10, 1–2 kg if medicine ball is used).	AMRAP 6 min: 8 rows, 10 jumps, 20 s plank	Moderate	Continuous
S5	Shoulder press or medicine ball chest press (2 × (8–10), 1–2 kg), with more complex variations only if technical criteria are met.	3 rounds: 10 presses, 15 jumps, 10 m run	Moderate	Continuous
S6	Lunges (2 × 8/leg). Progress depth and load if appropriate.	4 rounds: 8 lunges, 10 jumps, 10 m crawl.	Moderate	Continuous
S7	Jump squat (2 × 8).	AMRAP 8 min: 5 jump squats, 10 jumps, 10 m run.	Moderate–high	Continuous
S8	Medicine ball throw or push-press variation (2 × (8–10), 1–2 kg) if technical criteria are met.	4 rounds: 8 throws/presses, 12 lateral jumps, 20 m run.	Moderate–high	Continuous
S9	Kettlebell swing (2 × 8, 4–6 kg) only if hip-hinge competency and trunk control are consistently demonstrated, otherwise deadlift-pattern drill with wooden bar or light training bar.	AMRAP 8 min: deadlift-pattern reps or medicine ball slams, 10 squats, 15 m run.	Moderate–high	Continuous
S10	Goblet squat (2 × (8–10), 4–5 kg).	3 rounds: 10 squats, 15 jumps, 10 m duck walk.	Moderate–high	1 min between rounds
S11	Incline or standard push-ups (2 × (8–10)).	AMRAP 10 min: 5 push-ups, 10 m bear crawl, 10 tuck jumps.	Moderate–high	Continuous
S12	Loaded deadlift with wooden bar/light training bar (2 × (8–10)). Load progressed conservatively according to technique.	3 rounds: 10 deadlift-pattern reps, 15 m zigzag run, 8 squat thrusts or burpees if technically appropriate.	Moderate–high	30 s between rounds
S13	Dumbbell shoulder press (2 × 8, 2–3 kg total load). Progress load based on technique.	4 rounds: 8 lunges, 10 box step-ups/jumps, 10 m crawl.	Moderate–high	Continuous
S14	Jump squat (2 × 8).	AMRAP 8 min: 5 jump squats, 10 jumps, 10 m crab walk.	Moderate–high	Continuous
S15	Goblet squat (4–6 kg) or deadlift with light training bar (3 × (6–10)), depending on technical competency and planned progression.	3 rounds: 10 deadlift-pattern reps, 8 jumps, 10 m zigzag run	Moderate–high	30 s between rounds
S16	Jump lunges (2 × 8/leg) only if landing mechanics and unilateral control are adequate; otherwise alternating reverse lunges.	4 rounds: 8 jump lunges, 10 lateral jumps, 10 m bear crawl.	Moderate–high	Continuous

Note: AMRAP = as many rounds as possible; METCON = metabolic conditioning; Exercises involving external loads (e.g., kettlebell swing, goblet squat, and medicine ball variations) will only be introduced following confirmation of prerequisite movement competency by the supervising coach.

